## Abstract

**Background:**

The early diagnosis of cognitive impairments is an important step in the adequate management of dementia. The project “Smart Cognition & Behaviour Screening powered by Augmented Reality” (SCOBES-AR) aims to develop a multimodal screening tool (MST) for the early detection of cognitive impairments using augmented and virtual reality. The first project phase selected validated assessments for combination with the MST and tested it in 300 healthy older adults.

**Objective:**

This study established a protocol for the implementation and usability of a mixed reality (MR)–enhanced multidisciplinary screening tool for the early detection of cognitive impairments in older adults. The developed MST will be partially enhanced by MR, which is a combination of augmented reality (AR) and virtual reality (VR). This MR-enhanced prototype of the screening tool (MR-MST) will be tested and compared to the previously developed MST. The usability of the prototype will also be examined.

**Methods:**

This single-center observational crossover design study screens 100 healthy participants (aged 60-75 years) for cognitive decline using a specially developed MST (assessment of cognitive functions, olfactory sensitivity, nutritional preferences, gait parameters, reaction times, and activities of daily living) and an MR-enhanced MST in which the assessments of cognitive functions, reaction time, activities of daily living, and gait will be performed using tailor-made software and AR and VR hardware. The results of the MR-enhanced MST will be compared to those without MR. The usability of the developed MR-enhanced MST will be tested on 10 investigators and 10 test participants using observed summative evaluation and the codiscovery method, and on 2 usability experts using the codiscovery and cognitive walkthrough methods.

**Results:**

This study was funded by the Austrian Research Promotion Agency (grant 866873) and received approval from the ethics committee of the Medical University of Graz. The MR-MST and the experimental protocol for this study were developed. All participants gave written informed consent. As of July 15, 2022, a total of 70 participants have been screened. Data analysis and dissemination are scheduled for completion by September 2023.

**Conclusions:**

The development and testing of the MR-MST is an important step toward the establishment of the best practice procedure for the implementation of AR and VR in the screening of cognitive declines in older adults. It will help improve our knowledge of the usability and applicability of the developed prototype and promote further advancement in AR and VR technologies to be used in therapeutic settings.

**International Registered Report Identifier (IRRID):**

DERR1-10.2196/39513

## Introduction

Human neurocognitive functions decline with advanced age, but this decline may often exceed physiological cognitive aging and progress to dementia. The prevalence of dementia worldwide is expected to almost double every 20 years, from 46.8 million in 2015 to 131.5 million in 2050 [1], which poses an increasing challenge for health and social systems. On the way from normal cognitive decline to dementia, mild cognitive impairment (MCI) is regarded as a decline in the ability to learn new information or recall stored information [2]. MCI was detected in 10%-15% of the population older than 65 years and is regarded as a “window” in which suitable interventions may delay progression to dementia [3]. The possibility of slowing dementia raises awareness of this global health problem in the scientific and health communities, which involve a large spectrum of clinicians, neuropsychologists, dietologists, speech therapists, physiotherapists, and occupational therapists. Combating dementia has become a public health priority. In accordance with the global action plan of the World Health Organization against dementia [4], international research has focused on the identification and reduction of risk factors, development of prevention and therapeutic interventions, and early detection of cognitive decline [5].

Because of the complexity of dementia diseases, predicting the course of MCI is not always successful. However, the efforts of clinicians and health providers are focused on screening, early diagnosis, and identification of risk factors. Very early diagnosis of MCI enables health care providers to manage these factors or ideally to decrease the potential progression to dementia. Notably, the early detection of MCI signs increases patient awareness and self-management and encourages participation in clinical studies or prevention programs. Although the diagnosis of early dementia initially causes uncertainty [6], people affected by this diagnosis and their family caregivers report benefits of early detection [7]. Healthy populations, and especially people 60 years or older, tend to show increased intention and willingness to be screened for cognitive decline [8-11].

Screenings and preventive interventions among older at-risk individuals that target several modifiable risk factors were effective [12,13]. Current clinical diagnostic procedures, such as liquor diagnostics and imaging techniques [14-18], are highly important but are not suitable for population-based early detection. Therefore, alternative screening tools that provide a low-threshold, safe, and valid way are needed to detect subtle cognitive changes in the earliest clinical phase. Notably, the manifestation of MCI includes cognitive, motor, sensory, and behavioral domains. These complex characteristics require a miscellaneous assessment approach.

The screening tools for cognitive impairments are controversial because of their limitations when they are performed using pen and paper [19]. For example, the written form does not allow direct digitalization for further and automatic processing, and these tests do not resemble real-life situations. Therefore, the performance of screening tests using augmented reality (AR) and virtual reality (VR) technologies facilitate data recording and processing while simultaneously enabling multisensory interaction of the subject with a real environment. AR superimposes 3D virtual objects into the real environment, typically using a tablet or a smartphone [20], but VR offers the user a multisensory experience of a simulated 3D virtual world via head-mounted displays, such as Oculus Quest screening tools [21]. For screening tests that aim for the early detection of cognitive decline, an integration of multiple domains with smart technology solutions must be developed and examined to prove their usability and validity.

The rationale for the Smart Cognition & Behaviour Screening powered by Augmented Reality (SCOBES-AR) project [22] is based on evidence-based predictors and protective factors for cognitive decline to establish a suitable assessment instrument that may be easily implemented in a nonclinical environment. Therefore, a combination of validated assessments of cognitive, motor, and behavioral functions was tested in the first phase of the project on 300 individuals aged 60-75 years. The multimodal screening tool (MST) includes assessments of olfactory functions [23], specificity of nutritional behavior [24], changes in gait pattern [25] and reaction time [26], cognitive functions [27], and instrumental activities of daily living [28]. As a next step, the developed MST will be enhanced with mixed reality (MR) technologies (AR and VR), which will require the establishment and testing of the developed prototype. Some of the assessments in the MR-enhanced screening tool will be performed using specially developed software and suitable AR and VR hardware, such as smartphones mounted in Haori headsets (AR) and Oculus Quest 2 (VR) headsets. This single-center observational crossover design study aims to establish a protocol for the implementation and usability of a prototype screening tool for the early detection of cognitive impairments in older adults using an MR environment.

## Methods

### Study Design, Participants, and Recruitment Procedure

This study developed a protocol for a single-center observational crossover design study. Male and female volunteers (N=100) aged 60 to 75 years were recruited from the pool of participants who had participated in the previous phase of the project. The volunteers were invited to a second visit at the Health Perception Lab, FH JOANNEUM University of Applied Sciences. Assuming that the effects were larger than the previous project phase, an effect size of 0.35 was selected. Therefore, with α=.05 and β=.95, a sample size of approximately 100 participants was considered sufficient for this study. Feasibility reasons and recruitment experience were also considered for the laboratory setting and geographical region. The recruitment and enrolment process for participants with stringent inclusion criteria (ie, age 60-75 years; absence of movement; and visual, auditory, neurocognitive, and psychiatric disorders) lasted from March 2022 to April 2022. For recruitment, participants were contacted by email or telephone to obtain consent and make preliminary agreements for participation. The study procedure, including the application of the respective information and technology devices, was presented to the volunteers. Participants were excluded from the study if they developed 1 or more of the conditions described in Textbox 1.

Study exclusion criteria.Clinical diagnosis of mild cognitive impairment or dementiaClinical diagnosis of mental illness (eg, depression, psychosis)Reduced mobility (eg, walking aid, wheelchair)Aided hearing or visual impairmentParticipation in any other cognitive training study within the last 6 monthsPresent guardianship according to the provisions of the Austrian adult protection law

All selected volunteers are tested once with the MST and once with the MR-MST in a randomized order. An independent investigator executed the randomization plan using a computer-generated random numbers table.

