#### Reaction Time Test: Match 4 Point Test

Studies on reaction time demonstrated that a slowing of the reaction time and an increasing intraindividual performance variability represented an important marker for the presence of dementia and MCI [55-57]. The Match 4 Point Test evaluates the complex reactions (eye-hand, eye-leg, and eye-hand-leg reactions) in response to visual signals displayed in a randomized order. Studies on the reliability and validity of the test demonstrated good test-retest reliability (*r*=0.82) and an acceptable correlation for convergent validity (*r*=0.61) compared to the results of the visual reaction test S1 by Schuhfried [58,59]. The test in block B is performed using the Talent Diagnose System (Werthner Sport Consulting) [25]. The Talent Diagnose System implements 3 contact plates (2 for the hands and 1 ground contact plate marked for the right and left foot), placed on a table (hands) and under a table (feet). A laptop computer displays 20 visual signals. The test participant is in a standing position and is instructed to touch the relevant contact plates as fast as possible using the left/right hand/foot in response to the given visual signal. The MR-enhanced “Match 4 Point Test” is performed in block C using a Google Pixel 6 smartphone by running a tailor-made mobile app and using 4 Flic 2 (Shortcut Labs) buttons, which are connected with the smartphone via Bluetooth. This app displays visual signals in the form of black and white shapes. Depending on the color and position of the signal, participants push the Flic 2 buttons with their left/right hand/foot. The time taken to complete the task is recorded.

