### Outcome Parameters and Data Analysis

Statistical analyses will be performed to identify possible correlations between the different components of the MST and MR-enhanced MST. Spearman rank correlations (Spearman ρ) or product-moment correlations (Pearson correlations) will be calculated, depending on the distribution of the collected data. Multiple regression analyses will be conducted for cases of strong effects in the correlation between the MST and MR-enhanced MST. Descriptive statistics of the data will be presented as means and SDs. The level of significance is set at α=.05. The statistical data will be evaluated using SPSS (IBM Corp).

For usability assessment, usability experts will collect and analyze data from the video observations and questionnaires. The video observations will be evaluated using “Eisenhower's Urgent/Important Principle” [78]**,** in which items are classified as “not urgent” to “urgent” and as “not important” to “important.” The “urgent” and “important” items indicate higher needs of improvement. The questionnaires addressing the personal experiences with the screening procedure are based on a 5-point Likert scale, where 1 indicates “very good usability.”

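### Sizing and testing the MST versus MR-MST correlations against zero says little about how closely the two versions correspond; conclusions should rest on the estimate and its confidence interval

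*Protocol article*

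**What the plan says.** **Sample size** (Study Design, Participants, and Recruitment Procedure). "Assuming that the effects were larger than the previous project phase, an effect size of 0.35 was selected", and then "with α=.05 and β=.95, a sample size of approximately 100 participants was considered sufficient for this study". Neither the metric of the 0.35 nor the null value is named.

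**Analysis** (Outcome Parameters and Data Analysis). The purpose is given as "Statistical analyses will be performed to identify possible correlations between the different components of the MST and MR-enhanced MST". The method is "Spearman rank correlations (Spearman ρ) or product-moment correlations (Pearson correlations) will be calculated, depending on the distribution of the collected data". The only numerical criterion is "The level of significance is set at α=.05". One further sentence refers to the size of a correlation: "Multiple regression analyses will be conducted for cases of strong effects in the correlation between the MST and MR-enhanced MST". Strong is not defined there, and the condition only triggers a regression.

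**Design** (Study Procedure; Strengths and Limitations). Each participant takes the block B assessments conventionally and again in block C with mixed reality, in randomized order. The visit lasts about 130 minutes, with a 10-minute break between the two blocks. The stated reason for the design is to set MST results against MR-MST results.

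**A reference value** (Reaction Time Test: Match 4 Point Test). A correlation of 0.61 with another reaction test is described as "an acceptable correlation for convergent validity".

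**The concern.** When one person takes two versions of the same assessment in one visit, some positive correlation is to be expected before any data are seen. A test of zero correlation then asks a question whose answer is largely known. The useful question is how strong the correspondence is for each assessment, and the sizing does not address it.

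What is at stake is interpretation. A correlation can be clearly significant at this sample size and still be too weak to say that the mixed reality version ranks people much as the conventional one does. If p<.05 is the only yardstick, a close match and a loose one are reported alike.

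**Working it through.** **Inputs.** Effect size 0.35, α=.05, power .95 (the printed β=.95 only makes sense as 1−β) and n=100 come from the section on study design. Pearson or Spearman correlation at α=.05 comes from the section on data analysis. The value 0.61 comes from the section on the reaction test. Two assumptions are added: the test is two-sided, and the Fisher z approximation holds (Pearson correlation, bivariate normal data).

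**1. Reproduce the sample size.** For a test of ρ=0:

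n = ((z₀.₉₇₅ + z₀.₉₅)/atanh(r))² + 3 = ((1.960 + 1.645)/0.3654)² + 3 = 100.3

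This matches the stated figure of about 100. Other readings of 0.35 fit less well:

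| Reading of 0.35 (power .95) | n |
|---|---|
| Correlation against zero, two-sided | 100.3 |
| Correlation against zero, one-sided | 85 |
| Point-biserial correlation, two-sided | 96 |
| Paired t test, standardized difference 0.35, two-sided | 109 |
| Regression with f²=0.35, 1 to 10 predictors | 40 to 80 |

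The first row is the closest, and it is also the analysis that the article plans.

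**2. Smallest significant correlation at n=100.** With t₀.₉₇₅ on 98 degrees of freedom = 1.984:

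r = t/√(98 + t²) = 1.984/√(98 + 3.938) = 0.197

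Shared variance is 0.197² = 0.039, about 4%.

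**3. What an observed correlation supports at n=100.** The 95% interval is tanh(atanh(r) ± 1.96/√97), with half-width 0.199 on the z scale.

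| Observed r | Shared variance | 95% CI |
|---|---|---|
| 0.20 | 4% | 0.004 to 0.38 |
| 0.35 | 12% | 0.16 to 0.51 |
| 0.61 | 37% | 0.47 to 0.72 |

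The first two are significant, and their intervals lie wholly below 0.61.

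**4. The same point by simulation.** If the true correlation were 0.35, about 95% of studies of this size would be significant, while an observed value of 0.61 or more would occur in about 0.04% of them.

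**5. What a floor would cost.** Suppose support were claimed only when the lower 95% limit exceeds a floor ρ₀. Then power = Φ((atanh ρ − atanh ρ₀)·√97 − 1.96).

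| Floor | True ρ | Value in Φ( ) | Power at n=100 |
|---|---|---|---|
| 0.50 | 0.61 | (0.709 − 0.549)·9.849 − 1.96 = −0.39 | 35% |
| 0.50 | 0.70 | (0.867 − 0.549)·9.849 − 1.96 = 1.17 | 88% |
| 0.60 | 0.70 | (0.867 − 0.693)·9.849 − 1.96 = −0.24 | 40% |
| 0.60 | 0.78 | (1.045 − 0.693)·9.849 − 1.96 = 1.51 | 93% |

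The lower limit clears 0.50 once the observed r is about 0.63, and clears 0.60 at about 0.71. The two floors are illustrations and have no source in the article.

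**The case against.** **No pass rule exists.** A reader might infer that any correlation of 0.20 or more makes the mixed reality version pass, or that significance will be offered as proof that it can replace the MST. The article says neither. Its stated purpose for the analysis is exploratory, its aims are implementation, usability and comparison, and it concedes under Strengths and Limitations that the two sets of results may not be directly comparable. The remark in the Introduction about proving validity concerns such tools in general. This objection stands, and it limits the point to what a significant result can support.

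**The 0.61 is not a criterion.** It is a literature value for one component against a different device. A reader might take it, or the retest correlation of 0.78 quoted for the ETAM, as a threshold for the whole tool. The article does not support that, and only two of the six ETAM items are used here. This also stands; 0.61 serves only as a point of reference.

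**A moderate correlation has several explanations.** The sample is restricted to unimpaired people aged 60 to 75, which can lower correlations. The tasks also change: gaze and a button replace the pen, and a street scene replaces photographs. It would be too strong to say that 0.35 shows the two versions measure different things. It is equally true that p<.05 cannot separate these explanations.

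**The metric of 0.35 is inferred.** This is correct. The analysis may also cover correlations across different assessments, for which 0.35 would be unremarkable. The point concerns the matched pairs.

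**Thresholds and intervals may be left to a fuller document.** That is fair for detail, and no missing threshold is alleged. The sample size argument and the significance criterion are stated in the article, and both are directed at zero.

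**Conclusion.** The point holds as a matter of design choice. Read as a correlation test, the sizing gives high power to show something that is nearly a given for matched pairs, and it gives no information on the degree of correspondence, which is the comparison the design was built for. Significance begins at a correlation of about 0.20, and an observed value equal to the planning value would have an interval ending at 0.51.

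This rests on three assumptions: that 0.35 is a correlation tested two-sided against zero, which is inferred from the reproduced n; that the pairs in question are the same assessment in blocks B and C; and that the Pearson, bivariate normal approximation is adequate. Spearman correlations or capped Trail-Making times would shift the figures somewhat. The recruited number is not at fault, since 100 participants estimate a correlation with useful precision.

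**What to change.** 1. For each matched pair in blocks B and C, report the correlation (or ICC) with its 95% confidence interval. Draw conclusions about correspondence from the estimate and its lower limit, and not from p<.05 against zero.
2. Restate the justification of n=100 as precision, for example that an observed 0.61 would have a 95% interval of about 0.47 to 0.72. Name the metric, and correct β=.95 to a power of .95 wherever the present calculation is kept.
3. A floor is optional. If the investigators want one, it should be set per test before the data are analysed, because range restriction and task changes differ between tests. Its power should be stated over a range of true values, including the unfavourable ones in the working. The power of a rule based on the ICC or Spearman correlation was not calculated here and would need its own calculation.

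**Cost.** Changes to the analysis wording, with the same 100 participants. The article reports 70 screened and no results yet, so the change could be fixed before analysis. The downside is a stricter and possibly less favourable statement of results, and a floor would often fail a test whose true correlation is only modestly above it.

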### Indemnity

This study is not an intervention study and poses a low risk to participants. For some attendees, the test results may indicate a deviation in cognitive abilities, which suggests early cognitive decline. When this occurs, we provide a comprehensive medical consultation with the study’s clinical investigator to ensure further medical care and possibly determine a further diagnostic plan. Participants may report slight fatigue when participating in the different assessments. A short preventive break is taken after approximately half of the testing procedure.

Part of the screening procedure involves wearing a head-mounted display with VR, which may cause cybersickness [29]. Cybersickness is triggered by visual stimuli during exposure to the virtual environment and shares similar symptoms with motion sickness, including nausea, sweating, dizziness, and fatigue. To minimize the risk of cybersickness, the participants undergo screening in a static (sitting or standing) position. The participants could withdraw from the screening in case of cybersickness. Except for these considerations, no health risks or side effects are expected for the participants.

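### The sample-size sentence gives β=.95, which as written means 5% power; the figure of about 100 fits power (1-β)=.95, so the label is wrong and the number is not

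*Protocol article*

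**What the plan says.** The sample-size justification is in Methods, Study Design, Participants, and Recruitment Procedure. It says that "an effect size of 0.35 was selected" on the assumption that effects would be larger than in the previous project phase, and continues: "with α=.05 and β=.95, a sample size of approximately 100 participants was considered sufficient for this study". It adds that feasibility and recruitment experience were also considered. The sentence does not name the test, the metric of the 0.35 or the sidedness.

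The design is within-participant: "All selected volunteers are tested once with the MST and once with the MR-MST in a randomized order". For the analysis, Outcome Parameters and Data Analysis states: "Spearman rank correlations (Spearman ρ) or product-moment correlations (Pearson correlations) will be calculated, depending on the distribution of the collected data". It also says "The level of significance is set at α=.05". Under Indemnity, the article notes: "The participants could withdraw from the screening in case of cybersickness".

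**The concern.** By convention β is the probability of missing a true effect, and power is 1-β. A design with β=.95 would miss the assumed effect 19 times out of 20. The printed value is 0.95 where 0.05 must be meant, a ratio of 19, in the only sentence that justifies the sample size. A reader who takes the sentence at face value gets a wrong operating characteristic. A reader who corrects it still has to work backwards to find which calculation gives 100.

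What is at stake is the accuracy of a stated design parameter in a published protocol. The question for the check is whether the slip is confined to the label or has also affected the number of participants.

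**Working it through.** **Inputs.** From the sample-size sentence: effect size 0.35, α=.05, β printed as .95, N about 100. From the analysis section: Pearson or Spearman correlation at α=.05. Assumed, because the article does not state them: the 0.35 is a correlation, the null value is zero and the test is two-sided.

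**Step 1: reproduce the figure with power .95.** With Fisher's z, N = ((z₀.₉₇₅ + z_power) / atanh(r))² + 3.

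- atanh(0.35) = 0.3654
- N = ((1.960 + 1.645) / 0.3654)² + 3 = 97.3 + 3 = 100.3

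The exact bivariate-normal distribution of r gives N = 100. The stated figure is reproduced.

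**Step 2: take β=.95 literally.** Power is then 1 - .95 = .05, and z_power = -1.645.

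- N = ((1.960 - 1.645) / 0.3654)² + 3 = 0.74 + 3 = 3.7, so about 4

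The exact power of the two-sided test at N = 4 is already 6.9%. The literal reading cannot produce 100.

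**Step 3: margin at 100 pairs.** Fisher-z power is Φ(√(n-3) × atanh(0.35) - 1.960). At n = 100 this is Φ(9.849 × 0.3654 - 1.960) = Φ(1.639) = 94.9%. The exact calculation gives 95.1%. There is essentially nothing to spare.

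**Step 4: Spearman, which the plan permits.** There are two ways to read the assumed effect.

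- If 0.35 is the Spearman correlation itself, with variance 1.06/(n-3), power at n = 100 is Φ(√(97/1.06) × 0.3654 - 1.960) = Φ(1.536) = 93.8%.
- If the data are bivariate normal with a Pearson correlation of 0.35 and are analysed by Spearman, a simulation of 100,000 samples gives about 92.8%.

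So power is about 93-94%.

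**Step 5: Pearson with fewer complete pairs.** The counts are illustrative; the article gives no rate of loss.

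| Complete pairs | Power, Fisher z | Power, exact |
|---|---|---|
| 100 | 94.9% | 95.1% |
| 95 | 93.9% | 94.1% |
| 90 | 92.6% | 92.9% |
| 80 | 89.4% | 89.8% |

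Power falls by one to two points for each of the first two steps of five pairs, and is still about 90% at 80 pairs.

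**The case against.** The strongest reply is that nobody could be misled. Five per cent power is absurd as a design target, 100 is the right number for the evident intent, and writing β for 1-β is a familiar slip. The article speaks only of approximately 100 being sufficient and also cites feasibility, so it promises no exact 95%. As a condensed account, it may leave metric, sidedness and any allowance for losses to the full protocol. Most of this stands. It limits the severity and means that those omissions are not faults in themselves. It does not make the printed β correct.

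A reader might infer more than the documents support, in four ways.

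- **That the study is underpowered.** It is not shown to be: the two-sided Pearson test reaches 95% at 100 pairs.
- **That 95% holds for only one test, and an unnamed one.** Pearson correlation is named in the analysis section; it is missing only from the sample-size sentence. Other readings of 0.35 also reach 95% at 100, for example a one-sided correlation test (97.6%).
- **That a paired comparison of means falls short.** A two-sided paired t test with a standardised difference of 0.35 would have 93.4% power at 100, but the analysis section plans no such test.
- **That the 70 participants reported as screened by 15 July 2022 indicate the final number of pairs.** That is a progress count, not a forecast.

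Withdrawal for cybersickness is a foreseeable way to lose pairs, but no rate is given. Cybersickness is tied to the VR headset, which in block C is used for the ETAM, so a withdrawal need not remove a participant's other pairs.

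**Conclusion.** The sentence is wrong as written: "with α=.05 and β=.95" states 5% power, which is incompatible with a sample of about 100. The error is in the label. With power (1-β)=.95 the figure follows for a two-sided Pearson correlation of 0.35, so N stands.

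The remaining effect is small. Power is one to two points below 95% if Spearman is used at 100 pairs, and about two points below for Pearson if ten pairs were lost. These figures rest on the assumed metric and sidedness, on a null correlation of zero and on approximately bivariate normal data. That the authors ran this particular calculation is an inference from the match, not something the article says. Severity: minor.

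**What to change.** Replace β=.95 with power (1-β)=.95 (β=.05). This needs no further information.

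Ask the authors to confirm the underlying calculation and, if they do, add: the sample size is based on a two-sided test at α=.05 of a Pearson correlation of 0.35 against zero, for which about 100 complete pairs give 95% power. If the 0.35 was another metric, they should name that metric and its test instead.

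Add one clause saying that power is about 93-94% at 100 pairs under Spearman, and about 93% for Pearson at, say, 90 complete pairs, marked as illustrative.

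The cost is one corrected sentence and a slightly less favourable stated power. Enrolment, conduct and analysis do not change.
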